## Methods and analysis

### Data source

We will use data from 664 UK general practices contributing to the CPRD (http://www.cprd.com). The practices are spread across the UK, and their registered patients have been shown to be representative of the general population.^38^ Data are routinely collected and the recorded information includes demographics, patient characteristics, clinical diagnoses, symptoms and prescribed medications. The database has been validated using other sources of information in the UK and has been used for similar studies for statin discontinuation.^29^
^30^

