### Covariates

To describe the cohort and explore factors associated with the risk of discontinuation, we will consider the following covariates in six major groups. First, demographics will include age (<45; 45–54; 55–64; 65–74; 75–84 years), sex, ethnicity (Caucasian or not recorded, Indian, Pakistani, Bangladeshi, other Asian, Black African, Black Caribbean, Chinese, other ethnic group) and socioeconomic status as measured by the Townsend deprivation score in quintiles. Second, clinical values will include smoking status (non-smoker; ex-smoker; light smoker: <10 cigarettes/day; moderate smoker: 10–19 cigarettes/day; heavy smoker: 20+cigarettes/day; not recorded), body mass index (BMI) in kg/m^2^ (<25; 25–29.9; 30–34.9; 35+, not recorded), systolic blood pressure and cholesterol/high-density lipoprotein (HDL) ratio. Third, chronic diseases will include rheumatoid arthritis, chronic renal disease, liver disease, atrial fibrillation, treated hypertension, cancer, heart failure, diabetes and dementia. Fourth, genetic characteristics will include family history of premature coronary heart disease and diagnosis of familial hypercholesterolaemia. Fifth, other medications will include use of aspirin, use of anticoagulants and—as a proxy for comorbid conditions—the number of different types of medicines having systemic effect and associated with British National Formulary^39^ categories (in each case, at least one prescription in the last year before the entry date). Finally, only for patients in the primary prevention group, their 10-year cardiovascular risk as calculated by the QRISK2–2014 score (banded <5%; 5–9%; 10–14%; 15–19%; 20–24%; 25%+).

For clinical values, the most recently recorded value prior to or at the cohort entry will be used. Chronic diseases will be considered if they were recorded at or before the baseline. For the main analysis, we will use practice-based Townsend deprivation scores as these are available for the whole cohort. We will run an additional analysis on the subset of practices that have consented to link their data to Townsend scores at patient level.

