To explore the risks of statin discontinuation associated with the covariates, a Cox regression analysis will be undertaken. The model will include age, sex, ethnic group, deprivation quintile, calendar year at the entry to the cohort, baseline CVD risk and the type of statin prescribed at the baseline. Practices might differ in their prescription patterns, so we will account for clustering by practice. We shall calculate the adjusted HRs for baseline characteristics listed above: clinical values; chronic diseases; family history; use of other medications.

The proportional hazards assumption will be checked by using a log-log plot of survival for each variable. Variables which violate the assumption will be included into the model as a stratification factor. If clinically similar variables or categories (for smoking and ethnicity) are associated with similar risks, they will be combined. For continuous variables, recorded values will be used. For non-linear risk associations, fractional polynomials will be used if appropriate.^40^

As BMI, smoking status, systolic blood pressure and cholesterol/HDL ratio may be important patient characteristics but have non-negligible numbers of missing data, multiple imputation will be used to replace missing values.^41^ Five imputed data sets will be created, using multiple chained equations, and Rubin's rules will be used to combine effect estimates and SEs to allow for uncertainty due to imputing missing values. Calendar year; statin stopper status; log of survival time; age; years of records; potentially important characteristics; and type, dose and cumulative exposure to statins will be included in the imputation model.^42^

The main analyses will be run using the multiply imputed data. The least complete data are expected to be for cholesterol/HDL ratio, but information about this test is expected to be important for patient adherence. To ensure the robustness of our findings, we shall also run a sensitivity analysis including only patients with complete data.

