## Discussion

This is an observational study based on routinely collected data from a large primary care research database and will have the strengths and limitations common to such studies. The strengths include the representativeness of the study population, large size of the sample and substantial statistical power. Information about discontinuation rates is scarce, and no previous study has described discontinuation rates in the general population separately for primary and secondary prevention. Our paper will also report on a significantly longer follow-up time than previous studies.^27^
^28^

The limitations of the study will include potential overestimation of statin use. While we have precise dates on which prescriptions were issued, we do not have detailed information about whether patients took their pills, when they started and stopped taking the pills, or whether they followed the prescribed regime, although it is likely that most patients with more than one prescription were genuine users.^43^ There is also a possibility of underestimation of statin use because simvastatin has been available over-the-counter since 2004, and some patients might have obtained it without returning to the general practitioner for repeat prescriptions. These would appear as false stoppers, but a Health Survey for England has shown the proportion of patients using over-the-counter sources (restricted by license to individuals with a 10–15% 10-year CVD risk) to be very low at 0.2%.^44^ Another limitation is the lack of information on reasons for statin discontinuation, such as side effects or no further need for the drug. Although some of this information may be recorded, it is too sparse to be used in the analysis.

Not all of the possible factors associated with statin discontinuation, which have been reported by other studies, will be available for our analysis. Some of them might have proxies in the form of a similar association, for example, the social deprivation category in our study for levels of education or income. Other factors, such as the quality of communication between patient and doctor or the patient's understanding of information on statins^45^ are not recorded in primary care databases and would be infeasible to include in a large study of this kind.

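### The main deprivation HR compares practices, not patients, and the planned patient-level run changes the score and the set of practices together, so a gap between the two results cannot be attributed to either.

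*Protocol article*

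**What the plan says.** The Covariates section places deprivation among the demographics, as "socioeconomic status as measured by the Townsend deprivation score in quintiles". It then fixes the measure: "For the main analysis, we will use practice-based Townsend deprivation scores as these are available for the whole cohort". The follow-up is stated in one sentence: "We will run an additional analysis on the subset of practices that have consented to link their data to Townsend scores at patient level". The number of linked practices is not given.

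Under Statistical analysis, discontinuation rates are to be reported by deprivation quintile, and the quintile is a core Cox term: "The model will include age, sex, ethnic group, deprivation quintile, calendar year at the entry to the cohort". The same section adds: "Practices might differ in their prescription patterns, so we will account for clustering by practice".

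The Discussion says that some factors missing from the data may have proxies and offers as an example "the social deprivation category in our study for levels of education or income". Neither the strengths and limitations box nor the Discussion mentions that the main deprivation score belongs to the practice. The linked-practice run is not among the analyses under Sensitivity analyses, and the article does not say how its result will be set against the main one.

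**The concern.** The measure and its intended reading sit at different levels. The score ranks practices, while the stated aim and the education-or-income example concern patients. Patients within a practice differ in deprivation, so the top and bottom fifths of practices differ less in patient deprivation than the top and bottom fifths of patients do. A weak main HR could then partly reflect the measure rather than the absence of a patient-level association.

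The patient-level run is the natural place to find out, but as described it makes two changes at once: a different score and a different set of practices. At stake is whether the study can say anything about individual deprivation from its main model, and whether a reader can use the linked analysis to judge how far the main HR is diluted.

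**Working it through.** **The plan's own figures.** The article gives no effect size, power or correlation for deprivation; its sample size section concerns statin type only. There is no figure to reproduce. The one input used from the document is the number of practices: "We will use data from 664 UK general practices contributing to the CPRD", so 664 / 5 ≈ 133 practices per quintile if quintiles are cut over practices. Everything else below is an assumption, shown over a range.

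**Step 1: expected attenuation with no practice-level effect.** Let r be the correlation between practice and patient scores, both standardised and roughly normal, with a log-linear patient-level effect. Top and bottom quintile means of a standard normal score lie about 2.80 SD apart. Grouping by the practice score leaves a gap in patient score of r × 2.80, so

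log HR(practice score) ≈ r × log HR(patient score), or HR(practice) ≈ HR(patient)^r.

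| Assumed patient-level HR | Practice-score HR |
|---|---|
| 1.20 | 1.08 (r = 0.4), 1.12 (r = 0.6), 1.16 (r = 0.8) |
| 1.30 | 1.08 (r = 0.3), 1.14 (r = 0.5), 1.20 (r = 0.7), 1.27 (r = 0.9) |

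For example, exp(0.6 × ln 1.20) = 1.12.

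**Step 2: check by simulation.** Settings: 664 practices, 300 patients each, exponential times, patient score with SD 1, true patient-level HR 1.30, and between-practice share of score variance (ICC) of 0.25 or 0.5. HRs are event-rate ratios, top versus bottom quintile, without other covariates.

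- Practice score equal to the mean of its patients (r = √ICC = 0.50 or 0.71): 1.14 or 1.20.
- Practice score equal to that of the practice's own location (r = ICC = 0.25 or 0.50): 1.07 or 1.14.

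Both agree with the formula.

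**Step 3: add a practice-level effect.** This is a log HR per unit of practice mean, on top of the patient effect. The practice-mean score is used here.

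| Practice-level effect | ICC | Patient-score HR | Practice-score HR |
|---|---|---|---|
| +0.2 | 0.25 | 1.50 | 1.50 |
| +0.2 | 0.5 | 1.72 | 1.79 |
| −0.1 | 0.25 | 1.21 | 0.99 |
| −0.1 | 0.5 | 1.13 | 0.99 |

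The direction is therefore not fixed. The practice-score HR can equal or exceed the patient-score HR, or lose the association altogether.

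**Step 4: the two planned results and the missing one.** Assume 60% of practices are linked, ICC 0.5, true patient-level HR 1.30 in the unlinked practices and no separate practice-level effect.

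| True HR in linked practices | A: all practices, practice score | B: linked, practice score | C: linked, patient score |
|---|---|---|---|
| 1.10 | 1.122 | 1.070 | 1.098 |
| 1.30 | 1.208 | 1.207 | 1.300 |
| 1.50 | 1.276 | 1.331 | 1.496 |

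The article describes A and C. Their ratio C/A is the product of B/A (change of practices) and C/B (change of score):

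- 1.10: C/A = 0.979 = 0.954 × 1.026. A and C look alike although the practice score is attenuated.
- 1.30: C/A = 1.076, almost all of it from the score (B/A = 0.999, C/B = 1.077).
- 1.50: C/A = 1.172 = 1.043 × 1.124. Part of the gap comes from the practices.

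From A and C alone these cases cannot be told apart by cause. Adding B separates the two changes.

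**The case against.** The choice is stated openly, with its reason, and a patient-level analysis is already promised. Keeping the whole cohort in the main model and using the finer measure where it exists is an ordinary trade-off. Deprivation is one of many exploratory covariates, with no hypothesis or power claim attached, and the proxy remark in the Discussion is hedged and given as an example. All of this stands, and it is why the main analysis need not change.

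A reader might infer that the practice score necessarily shrinks the contrast. The documents do not support that: Step 3 shows that a practice-level effect can move the HR either way, and the article itself expects practices to differ in prescribing.

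A reader might also infer that the two planned results cannot be compared at all. That is too strong. If linked practices resemble the rest, the plain comparison is informative (second row of Step 4), and the masking in the first row needs an assumed difference between practices for which the article gives no basis. The patient-level HR is in any case a direct estimate of the patient-level association in the linked practices, and the article does not present it as a validation of the main HR.

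Finally, the condensed article does not rule out refitting the practice score in the linked practices, and the full plan may include it. That limits the complaint about the missing model. It does not remove the mismatch between a practice-level measure and a patient-level reading, which the stated limitations leave unmentioned.

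**Conclusion.** The point holds in a limited form. The main deprivation HR is a contrast between practices' Townsend scores. As a measure of patient deprivation it is likely to be attenuated, with the log HR multiplied by roughly r if there is no separate practice-level effect. An assumed HR of 1.20 then appears as 1.16 to 1.08 for r from 0.8 to 0.4. Both the HR and r are assumptions, and the calculation ignores the other covariates and clustering.

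As described, the linked analysis changes score and practices together. A difference between the two HRs cannot be assigned to either cause, and agreement could hide attenuation if linked practices differ from the rest. This is a cheap improvement to what the study can conclude about deprivation. It is not an error that undermines the main analysis.

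**What to change.** - In the linked practices, fit the same Cox model to the same patients twice, once with practice-based and once with patient-level quintiles. Report both HRs beside the full-cohort HR.
- Draw conclusions about individual deprivation from the patient-level HR.
- Label the full-cohort HR as practice-level deprivation.
- Add the practice-level score to the limitations in the Discussion.

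The cost is one further model in the linked practices (fitted in each prevention group, as all analyses are), with no new data. The price in precision is that the individual-level conclusion rests on the smaller linked subset. The main analysis stays as planned.

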### Statistical analysis

All analyses will be performed separately for the subgroups with and without a diagnosis of CVD at the study entry date.

The numbers of incident users who stop statins will be reported and the rate of discontinuation will be assessed by dividing the number of incident stoppers by the number of person-years. The rates will be calculated overall and by calendar year, ethnic group, deprivation quintile, initial statin type, and baseline risk of CVD (for primary prevention group). We shall also calculate the percentages of patients who switch between different statins during the study period, considering a patient as a switcher if their type of statin (ingredient) changed during their follow-up. For patients in the primary prevention group who were diagnosed with CVD after entering the study, we shall report the percentages of patients who continued using statins after the diagnosis.

We shall report general descriptive statistics such as average duration of statin therapy before discontinuation, proportions of patients who had their last statin prescription within 6 months, 6 months to 1 year, 1–5 years or more than 5 years after their first prescription, and graphically summarise the data using Kaplan-Meier curves. As we expect different rates of discontinuation for short-term (less than 12 months between the first and the last prescription) and long-term (more than 12 months between the first and the last prescriptions) users, we shall calculate rates by term of use.

For those patients who discontinued statins and for those who did not, summary statistics will be calculated for the baseline covariates. We shall report frequencies and proportions for categorical data, and for continuous data, suggested bands as well as means (SD), medians and ranges. We shall also report the type of statin, the potency, calendar year for the baseline, cumulative duration of exposure before leaving the cohort (defined as the time interval between the first prescription and expected end date for the last prescription), and whether the patient had switched statin type during the study period. We shall calculate the survival-time function, report the descriptive statistics such as median duration, plot Kaplan-Meier curves for the covariates and compare the survivor functions for the covariates using the log-rank test.

To explore the risks of statin discontinuation associated with the covariates, a Cox regression analysis will be undertaken. The model will include age, sex, ethnic group, deprivation quintile, calendar year at the entry to the cohort, baseline CVD risk and the type of statin prescribed at the baseline. Practices might differ in their prescription patterns, so we will account for clustering by practice. We shall calculate the adjusted HRs for baseline characteristics listed above: clinical values; chronic diseases; family history; use of other medications.

The proportional hazards assumption will be checked by using a log-log plot of survival for each variable. Variables which violate the assumption will be included into the model as a stratification factor. If clinically similar variables or categories (for smoking and ethnicity) are associated with similar risks, they will be combined. For continuous variables, recorded values will be used. For non-linear risk associations, fractional polynomials will be used if appropriate.^40^

As BMI, smoking status, systolic blood pressure and cholesterol/HDL ratio may be important patient characteristics but have non-negligible numbers of missing data, multiple imputation will be used to replace missing values.^41^ Five imputed data sets will be created, using multiple chained equations, and Rubin's rules will be used to combine effect estimates and SEs to allow for uncertainty due to imputing missing values. Calendar year; statin stopper status; log of survival time; age; years of records; potentially important characteristics; and type, dose and cumulative exposure to statins will be included in the imputation model.^42^

The main analyses will be run using the multiply imputed data. The least complete data are expected to be for cholesterol/HDL ratio, but information about this test is expected to be important for patient adherence. To ensure the robustness of our findings, we shall also run a sensitivity analysis including only patients with complete data.

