Of these, all seem to have concentrated on patients with already diagnosed CVD, and most were conducted either before the most recent CVD guidelines were issued or UK-derived CVD risk estimation was available. One study, based on Clinical Practice Research Database (CPRD) data, which showed an association between discontinuation and higher total mortality following acute myocardial infarction,^29^ has also provided information about prevalence of comorbidities with respect to different patterns of statin use. Another CPRD study has investigated the factors associated with discontinuation,^30^ but this study was conducted in 2002. This assessed discontinuation risks in a mixed group of patients, but having only 20% of the cohort without diagnosed CVD and following up patients for only 1 year. It has also been noted that further research is needed particularly for patients with low cardiovascular risk.^31^

While there have been observational studies examining the pattern of uptake of statins^32–34^ and of unintended effects from statin use,^35–37^ relatively few studies have examined the discontinuation of statins. We have, therefore, designed a study that will follow statin users in the UK over time, report the rates of stopping for statins with the discontinuation outcome based on prescription data, and look at whether these have changed with time or differ across statin types. The study will also identify any patient groups more likely to stop statins and so possibly increase their risk of CVD.

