### Sample selection

This will be a prospective open cohort study of new statin users identified during the study period between 1 January 2002 and 30 September 2013. Incident cases who discontinued statin therapy will be identified during follow-up. Patients will enter the cohort on the date of their first recorded statin prescription within the study inclusion period. Patients will be followed up until the earliest of: death; deregistration with the practice; last upload of computerised data; 1 year from the date the study inclusion period ended. Patients will be subdivided into two groups evaluated on the date when they started taking statins: those without CVD records before the entry date (taking statins for primary prevention); those with CVD diagnosed at or before entering the study (taking statins for secondary prevention). Patients without CVD at the baseline date will be followed up until the time of a CVD diagnosis if it occurs before the study exit date.

We expect the rate of discontinuation to be lower in the secondary prevention group, and this subdivision will make our results more easily comparable with existing studies.

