### Inclusion criteria

Eligible patients will be aged 25–84 years at the study entry, have at least two prescriptions for a statin in the study period and have at least 1 year of records prior to entry—calculated from the later date of: the date of registering with a general practice or the earliest date of upload of computerised practice data—and at least 1 year of follow-up—calculated from their first statin prescription in the study period. Patients with one or more prescriptions for statins in the 12 months prior to cohort entry will be excluded. Cerivastatin will not be included in the study because it was withdrawn from the market in August 2001, but patients with prescriptions for it in the 12 months prior to cohort entry will be excluded.

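### Crude discontinuation rates by calendar year mix calendar time with time since starting a statin, so they can show a trend when stopping behaviour has not changed

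*Protocol article*

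**What the plan says.** Under Statistical analysis, "the rate of discontinuation will be assessed by dividing the number of incident stoppers by the number of person-years". The breakdown is one-way: "The rates will be calculated overall and by calendar year, ethnic group, deprivation quintile, initial statin type". The section does not say whether calendar year is the year in which person-time falls or the year of entry.

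The cohort is described under Sample selection and Inclusion criteria:
- It consists of "new statin users identified during the study period between 1 January 2002 and 30 September 2013".
- Time at risk starts at the first prescription: "Patients will enter the cohort on the date of their first recorded statin prescription within the study inclusion period".
- Recent users are removed: "Patients with one or more prescriptions for statins in the 12 months prior to cohort entry will be excluded".
- Follow-up stops at the latest "1 year from the date the study inclusion period ended", that is, 30 September 2014.
- The main analysis requires at least two prescriptions.

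The Introduction gives the purpose of the rates: to report them and "look at whether these have changed with time or differ across statin types".

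Statistical analysis also says that rates are expected to differ between users of less than and more than 12 months, and plans rates by term of use. It does not cross these with calendar year. The Cox model includes calendar year at entry. Additional analyses reruns the main analysis censored at the end of year 1, and again without year-1 stoppers.

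**The concern.** In an open cohort built only from new users, calendar year and time since starting are tied together. In 2002 everyone at risk is in the first year of use. Each later year holds a larger share of longer-term users, and after 30 September 2013 nobody enters. If the hazard of stopping varies with time since starting, which the protocol expects, a crude calendar-year rate moves with this mix.

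Whether stopping has changed over time is a stated aim, and the Introduction motivates it with the 2006 and 2014 guideline changes and with publicity about side effects. The Introduction also expects stopping to rise as lower-risk patients are treated. An artefactual fall by year of follow-up could hide such a rise. An artefactual rise by year of entry could be taken for one.

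**Working it through.** The article states no calendar-year rate, so there is no figure to reproduce. The check asks what the planned estimator returns when behaviour does not change.

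**Inputs from the article.** Entry 1 January 2002 to 30 September 2013, follow-up to 30 September 2014, first discontinuation only, rate = events / person-years.

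**Assumptions, not in the article.** Uniform entry; 5% a year exit for other reasons; a hazard that depends only on time since first prescription, with one value in year 1 and another after. The pairs, per 100 person-years (PY), are:
- 30 then 15.
- 71.3 then 15. The first value turns the 49% one-year adherence quoted in the Introduction for observational studies into a hazard: -ln(0.49) = 0.713.
- 20 throughout.

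Two further runs allow no event in the first 56 days. This is a rough stand-in for the two-prescription rule, assuming 28-day prescriptions. The one-year minimum follow-up rule was not modelled.

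**Formula.** If p is the share of a year's person-time that is first-year use, the crude rate is p × h1 + (1 - p) × h2. For 30 then 15 this is 15 + 15p:
- 2002: 15 + 15 × 1.000 = 30.0
- 2004: 15 + 15 × 0.480 = 22.2
- 2013: 15 + 15 × 0.208 = 18.1
- 2014: 15 + 15 × 0.083 = 16.2

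**By year of follow-up (per 100 PY, behaviour unchanged).** The column for p refers to 30/15.

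| Year | p | 30/15 | 30/15, 56 days event-free | 71.3/15 | 20/20 | 20/20, 56 days event-free |
|---|---|---|---|---|---|---|
| 2002 | 100% | 30.0 | 20.9 | 71.3 | 20.0 | 14.1 |
| 2003 | 71.5% | 25.7 | 22.0 | 57.8 | 20.0 | 17.6 |
| 2004 | 48.0% | 22.2 | 19.7 | 45.2 | 20.0 | 18.4 |
| 2007 | 28.8% | 19.3 | 17.8 | 33.9 | 20.0 | 19.0 |
| 2012 | 22.0% | 18.3 | 17.1 | 29.7 | 20.0 | 19.2 |
| 2013 | 20.8% | 18.1 | 17.2 | 28.9 | 20.0 | 19.3 |
| 2014 | 8.3% | 16.2 | 16.2 | 20.2 | 20.0 | 20.0 |

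**By year of entry.** For 30/15: 18.2 (2002), 18.6 (2006), 20.0 (2010), 22.8 (2012), 26.5 (2013). Later entrants have shorter follow-up, so more of their person-time is first-year use. For 71.3/15: 29.2 to 60.4. For 20/20: flat.

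**Sensitivity, 30/15.** The 2013/2002 ratio is 18.1/30.0 = 0.60. With entry growing or shrinking by 10% a year it is 0.64 or 0.57. With 7% a year exit the 2014 rate is 16.4, and no other 30/15 figure above moves by more than 0.2.

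**After banding.** Within each band (under 1 year, 1 year or more) the rates in the runs without an event-free start are constant across calendar years by construction, at 30 and 15 in the first case.

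**The case against.** The strongest reply is that the plan already examines time with duration held fixed. In a Cox model on time since first prescription, risk sets compare patients at equal duration. If the hazard is h0(t) × exp(b × (entry + t)), the exp(b × t) part goes into the baseline and the entry-year coefficient estimates b without this artefact. The rerun censored at year 1 gives adjusted first-year stopping by entry year. No trend test on the crude rates is announced. All of this stands, provided the model runs on time since entry, which the article implies but does not state. A reader might infer that the aim is left unanswered or that the Cox result is contaminated; the document does not support that. The Cox term nevertheless does not correct the tabulated rates, and it is the rates themselves that the Introduction wants to compare over time.

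A reader might also infer that a fall is certain. It is not. The protocol expects different rates by duration and does not say that early stopping is higher. A constant hazard from day 0 gives no trend. With a 56-day event-free start, 30/15 first rises (20.9 to 22.0) and then falls to about 17, while a constant 20 rises from 14.1 to 19.3. Under 30/15, the change from 2007 to 2013 is only 19.3 to 18.1, about 6%.

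The planned rates by term of use do not help. They are not crossed with calendar year, and term is set by the last prescription, which lies close to the outcome, so time at risk is not split.

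Finally, a condensed article may leave table layout to a fuller document. That would excuse an omission. Here the estimator and its one-way breakdown are stated, and as stated they confound.

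**Conclusion.** The point holds for the crude calendar-year rates and goes no further. Crude stoppers per person-year by calendar year, in this new-user cohort, can show a trend with unchanged behaviour. The condition is a hazard that varies with time since starting, which the protocol itself expects.

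The direction depends on the shape of the hazard and on which calendar year is meant. Under 30 then 15 per 100 PY, the rate by year of follow-up falls to 0.60 of its 2002 value by 2013. Of that fall of 30.0 - 18.1 = 11.9, the first five years (2002 to 2006, 30.0 to 19.8) account for 10.2. A further drop follows in 2014, when entry has closed. By year of entry the rate rises by a factor of 26.5/18.2 = 1.46. With the assumed event-free start, the 2013/2002 ratio by year of follow-up is 17.2/20.9 = 0.82.

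The mechanism follows from the stated design. The sizes rest on assumed hazards, accrual and exit rates and are illustrations, not forecasts. No planned Cox result is shown to be wrong.

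**What to change.** 1. State whether calendar year in the rate tables is year of follow-up or year of entry.
2. Report calendar-year rates within bands of time since first prescription (under 1, 1-5, over 5 years), or standardised to a fixed distribution of those bands. Alternatively, report 1-year Kaplan-Meier stopping by entry year.
3. Base any statement about change over time on these figures and on the Cox entry-year hazard ratio. If the crude calendar-year rates are kept, label them as descriptive and not comparable across years.
4. Do not add time-updated calendar period to the Cox model alongside entry year. Calendar date equals entry date plus time since entry, so within a risk set their linear parts are collinear.

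Cost: a short addition to the text, one extra split of follow-up time and a few more table rows. No new data are needed.
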